#### Plans to promote participant retention and complete follow-up {18b}

Data collection protocols are designed to have a low burden of participation. For aims 1 and 2, active participation will entail one or two appointments at the research lab (after having been cast and fitted for a prosthetic socket). For aim 3, participation requires a small number of follow-up visits and is otherwise compatible with participants’ everyday life without restrictions. The reimbursement schedule follows the data collection/follow-up schedule to encourage the completion of the program.

#### Data management {19}

Data will be managed by the study statistician, who will work with the Biodynamics Lab staff to create the web-based application for data entry in collaboration with the study PIs. The statistician will also be responsible for monitoring data quality as the study is ongoing and merging any data not directly entered into a combined database for the study. Additional details related to the data management plan can be found in the Data Management section of this application.

#### Confidentiality {27}

The research lab is in an access-controlled building to which only research personnel have access. No sensitive or confidential information will be collected. All collected data will be de-identified and stored under a study ID, with the only document linking this ID to participant information being the consent form, which will be stored in a separate location from the data files. Electronic data storage complies with all applicable cybersecurity guidelines to prevent unauthorized access.

#### Plans for collection, laboratory evaluation, and storage of biological specimens for genetic or molecular analysis in this trial/future use {33}

No biological specimens will be obtained or stored for this study.

## Statistical methods

### Statistical methods for primary and secondary outcomes {20a}

#### Aim 1

The effects of in-socket mechanics, such as residual bone motion, peak skin strain, and pressure distribution on both physical function and patient-reported outcomes will be assessed using a generalized linear model (GLM). We will examine the effect(s) of each in-socket mechanical parameter on outcomes by utilizing the type III sum of squares tables. If our sample size drops below 30, we will develop separate models for each of the parameters of interest and outcome. Finally, we will create a unified model, containing the statistically significant parameter coefficients, which will allow us to predict physical function and patient response based on the changes to the included parameter estimates.

#### Aim 2

We will use partial correlation to examine the association between residual femur motion, skin strain, pressure, and readily available clinical measurements, while adjusting for potential confounders such as residual femur length (derived from CT data), overall residual limb length (measured from ischial tuber to distal end of the limb by caliper), contraction potential (tape measured as the difference of circumferential volumes during thigh muscle contraction and relaxation), and soft-tissue coverage (measured as a ratio between thigh and femur diameter). Partial correlation is a measure of the strength and direction of a linear relationship between two continuous variables whilst controlling for the effect of one or more other continuous variables (also known as “covariates” or “control” variables). Although partial correlation does not make the distinction between independent and dependent variables, the two variables are often considered in such a manner (i.e., you have one continuous dependent variable and one continuous independent variable, as well as one or more continuous control variables). If data is not approximately normal, we will use log transformations. Moderate-to-strong, significant correlations between research-grade and clinical data will be retained for empirical testing in aim 3.

#### Aim 3

Statistical analysis for aim 3 will involve two parts. First, the predictive model developed in aims 1 and 2 will be tested using data from 15 new participants (i.e., data not used to create the model). Second, we will compare the quantitative socket design to the current standard of care, in terms of patient outcomes and cost.

As part of the pilot clinical trial, we will use empirical data to test the socket modification model(s) created in aim 1 and clinical measure correlations obtained in aim 2. When empirical data are used to evaluate the model, there are several conventional statistical tests that can be applied to test the null hypothesis that the model output is wrong. These involve showing that some form of the predicted value does not equal the same form of the observed value (e.g., typical predicted, typical observed). The simplest empirical comparison is that of a regression of observed values on predicted values. We will obtain data as described for aims 1 and 2 on an additional 15 transfemoral prosthesis users using their current sockets and the sockets designed as part of the standard of care and through the new quantitative design process.

In order to compare the two methods of socket design (the quantitative design method compared to Standard of Care), we will compare patient-reported outcomes and cost between the two methods, utilizing the Wilcoxon-Mann-Whitney non-parametric test. Socket Comfort Scores (SCS, a simple patient-reported comfort score from 0 to 10) will be used to evaluate patient outcomes after wearing the two sockets. The SCS are reported to have a standard deviation of 2.3 points [50], meaning we will be powered to detect a difference of 1.1 points in the SCS given our sample size. With regard to costs, we will compare the two design approaches on the number of visits, cost of materials, and total cost of labor needed to develop the new socket. These costs will be recorded by the study prosthetist in his practice for the standard of care and in the Biodynamics Lab for the quantitative design method.

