#### Sample size {14}

To facilitate aims 1 and 2, GLM will be utilized, which is a flexible generalization of ordinary linear regression that allows for response variables that have error distribution models other than a normal distribution and is often robust to smaller sample sizes. With a sample size of *n* = 30 at 80% power and *α* = .05, we should be able to detect a moderate-to-large overall model effect (*f*^2^ = 0.45), while including all three in-socket mechanics. We will examine the effect(s) of each in-socket mechanical parameter on outcomes by utilizing the type III sum of squares tables. If our sample size drops below 30, we will develop separate models for each of the parameters of interest and outcome.

For aim 3, in order to compare the two methods of socket design (the quantitative design method compared to standard of care), we will compare patient-reported outcomes and cost between the two methods, utilizing the Wilcoxon-Mann-Whitney non-parametric test. With a sample size of *n* = 15 at 80% power and *α* = .05, we will be adequately powered to detect a moderate-to-large effect (*d* = 0.476) with respect to the differences in patient-reported outcomes and cost by method.

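### Aim 1 drops its mutually adjusted three-mechanic model once n falls below 30, although the plan's own power figure does not need that switch

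*Protocol article*

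**What the plan says.** The Sample size section {14} of the protocol article gives the basis for aims 1 and 2: "With a sample size of *n* = 30 at 80% power and *α* = .05, we should be able to detect" an overall model effect of f² = 0.45 with all three in-socket mechanics in the model. It states no allowance for losses.

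The Aim 1 paragraph of the statistical methods {20a} sets the test for each mechanic: "We will examine the effect(s) of each in-socket mechanical parameter on outcomes by utilizing the type III sum of squares tables". In a model holding all three mechanics, a type III test assesses each one adjusted for the other two.

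Both sections then carry the same switch: "If our sample size drops below 30, we will develop separate models for each of the parameters of interest and outcome". Nothing is said about adjusting those separate models for the remaining mechanics.

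The Aim 1 paragraph ends with a prediction step: "we will create a unified model, containing the statistically significant parameter coefficients". Under Aim 3, "the predictive model developed in aims 1 and 2 will be tested using data from 15 new participants".

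**The concern.** The planned size and the trigger are the same number, so on the stated figures any single loss changes the analysis. The change is one of substance. At n = 30 the question is what each mechanic contributes given the other two; at n = 29 it is how each relates to the outcome when the other two are ignored. Results from the two are not interchangeable, and a chance event should not decide which one is reported.

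The abstract says the socket changes are likely to alter residual limb motion, skin strain and pressure distribution, so correlation among the three is plausible. Where it exists, an unadjusted model can credit a mechanic that has no effect of its own. Aim 1 states a separate hypothesis for each mechanic, and its results feed the socket design process evaluated in aim 3, so it matters which mechanic receives the credit.

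**Working it through.** **Inputs from the article.** n = 30, α = 0.05, power 80%, f² = 0.45, three mechanics (Sample size {14}). f² = 0.45 corresponds to R² = 0.45/1.45 = 0.31.

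**Inputs assumed.** Loss rates of 2%, 5% and 10%; a common correlation among mechanics of 0, 0.3, 0.5 or 0.7; one row per participant. The article gives none of these.

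**1. Reproducing the plan's figure.** For the overall F test, power = P(F′ > F crit), where F′ is noncentral F with df1 = 3, df2 = n − 4 and λ = f² × n. At n = 30, df2 = 26 and λ = 0.45 × 30 = 13.5, giving 82.7%. The smallest n with at least 80% is 29, so the stated n = 30 is confirmed. The more conservative λ = f² × (n − 3) = 12.15 gives 78.1% at n = 30, close to the stated 80%.

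**2. The joint model below 30.** Same formula:

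| n | df2 | λ = 0.45n | Power |
|---|---|---|---|
| 30 | 26 | 13.50 | 82.7% |
| 29 | 25 | 13.05 | 81.0% |
| 28 | 24 | 12.60 | 79.2% |
| 27 | 23 | 12.15 | 77.2% |

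The first loss costs 82.7 − 81.0 = 1.7 points, and three losses cost 82.7 − 77.2 = 5.5 points. Nothing abrupt happens at 30.

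**3. How easily the rule fires.** If exactly 30 are enrolled and each is lost independently with probability p, the chance of fewer than 30 is 1 − (1 − p)^30. This is 45% at p = 2%, 79% at 5% and 96% at 10%.

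**4. What the switch does to attribution.** Simulation at n = 29 with three equally correlated mechanics, only the first active: y = √0.45 × x1 + e. The inert mechanic x2 is tested at 5%, alone and jointly; the active mechanic x1 likewise. Figures vary by a point or two between runs.

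| Correlation | Inert, separate | Inert, joint | Active, separate | Active, joint |
|---|---|---|---|---|
| 0.3 | about 14% | about 5% | about 90% | about 84% |
| 0.5 | about 31% | about 5% | about 90% | about 75% |
| 0.7 | about 58% | about 5% | about 90% | about 56% |

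At zero correlation the inert mechanic is flagged in about 5% either way.

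**5. The prediction step.** In the same scenario, screening by separate models and refitting the retained terms gave an apparent R² of about 0.36 and an R² of 0.23 to 0.25 in new participants. Keeping all three terms unselected and unshrunken gave 0.20. In a separate run, ridge with leave-one-out tuning gave 0.19 to 0.21, against 0.21 to 0.23 for screen-and-refit. With three truly active mechanics (effects of 0.3, correlation 0.3) the order reversed: 0.20 for ridge against 0.15.

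**The case against.** **Separate models have a real advantage.** Each mechanic is judged by its own type III test, not only by the overall F test. When mechanics are correlated, the joint model detects the active one less often, by 90 − 84 = 6 points at correlation 0.3 and 90 − 56 = 34 points at 0.7. This stands as a cost. It is not a reason for a threshold at 30, because the joint analysis planned at n = 30 already carries it.

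**The hypotheses speak of association.** An unadjusted model answers whether a mechanic is associated with comfort and function, and a correlated mechanic is then not a false positive. This stands in part. The Aim 1 methods also speak of effects and specify type III tests, and the question asked should not depend on whether 29 or 30 people finish. Reporting both analyses meets the point.

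**The unified model may restore adjustment.** If the retained terms are refitted together, an inert mechanic stays significant in only about 5% of runs. A reader might infer from the 14%, 31% and 58% that inert mechanics would be declared drivers of comfort in the final model. The documents do not support that: these are rates at the separate-model stage, under assumed correlations. An inert term that passes the screen does, however, remain in the equation.

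**Enrolment may exceed 30.** The full protocol may allow for losses, and aims 1 and 2 need only one or two laboratory visits. This is fair: the article states no allowance, which is not proof that none exists.

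**The trial is exploratory.** Aim 3 is a pilot, and its 15 new participants can reveal a poor prediction model. That is true, although the test comes only once the aim 3 sockets are being designed from the findings.

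**Conclusion.** The switch below n = 30 is not justified by the plan's own power figure and should go. The joint model keeps 81.0% power at n = 29 and 77.2% at n = 27, while the rule replaces adjusted effects with unadjusted ones on the loss of a single participant. This part rests only on the article's figures and the standard F-test calculation.

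The harm to attribution is conditional. It needs correlation among the mechanics, which is plausible but not given, and it vanishes at zero correlation. The simulation uses one row per participant. The trial tests 9 sockets per participant, and the article does not say how those rows enter the model, so the percentages illustrate the mechanism and do not forecast this trial.

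A reader might also infer that choosing terms by significance leaves aim 3 with an overfitted predictor that shrinkage would repair. That is not shown. With three candidates and one active mechanic, neither the unselected model nor ridge predicted better in new participants; with three active mechanics ridge did. The benefit depends on a truth the documents do not give.

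**What to change.** Delete the below-30 sentence in both the Sample size section and the Aim 1 methods. State instead that the joint three-mechanic model with type III tests is the main aim 1 analysis at whatever n is reached, and that single-mechanic models are reported as supplementary, unadjusted associations.

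The change is wording only. Its statistical price is a few points of overall power if a few participants are lost (1.7 for one, 5.5 for three), and per-mechanic power of about 84%, 75% or 56% instead of about 90% at assumed correlations of 0.3, 0.5 or 0.7.

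As a secondary suggestion, do not choose the terms of the prediction model by p-value alone, and report its leave-one-participant-out error before it is frozen for aim 3. This takes minor analysis work.

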#### Specific aim 3: Develop and evaluate an improved socket design and optimization process through the use of a predictive model based upon clinical measurements

In order to generate preliminary evidence on the clinical utility of the findings from aims 1 and 2, we will perform a pilot trial, using new subjects, to compare our data-informed optimization process resulting from aim 2 to the conventional iterative process for selecting a socket design and then optimizing the socket fit and function. We hypothesize that the data-informed method is advantageous in terms of (H1) patient-reported outcomes and (H2) cost, defined by the number of visits and socket iterations, and the amount of labor required to optimize the socket fit and function.

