**Fig. 6 Fig6:**
[figure not shown]
Flowchart showing the relationship between aims 1 and 2 (green background) and the pilot clinical trial, aim 3 (orange background). As an example, the flowchart shows three clinical measurements identified in aim 2 that correlate to in-socket mechanics obtained from research-grade measurements. In this example, those three clinical measures will then be used as predictors to guide the quantitative socket design

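### Aim 2 ends in partial correlations selected on r and p, but aim 3 needs predicted values from clinical measurements, and no analysis in the protocol produces them

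*Protocol article*

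**What the plan says.** Under Statistical methods {20a}, Aim 2, the protocol article names one method: "We will use partial correlation to examine the association between residual femur motion, skin strain, pressure, and readily available clinical measurements". The adjustment is for residual femur length (from CT), overall residual limb length (caliper), contraction potential (tape) and soft-tissue coverage (a thigh-to-femur diameter ratio). The same paragraph notes that "partial correlation does not make the distinction between independent and dependent variables". It closes with the retention rule: "Moderate-to-strong, significant correlations between research-grade and clinical data will be retained for empirical testing in aim 3". No numerical limit is attached to the size of r, and prediction error is not mentioned.

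The title of Specific aim 3 is "Develop and evaluate an improved socket design and optimization process through the use of a predictive model based upon clinical measurements". The Fig. 6 legend, working through an illustrative case, says that "those three clinical measures will then be used as predictors to guide the quantitative socket design". Under {20a}, Aim 3, "the predictive model developed in aims 1 and 2 will be tested using data from 15 new participants", and the simplest comparison offered is a regression of observed on predicted values. That section describes what comes from aim 2 as correlations and what comes from aim 1 as models. For aim 1, "we will create a unified model, containing the statistically significant parameter coefficients"; the parameters concerned are residual bone motion, skin strain and pressure.

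**The concern.** Designing a socket from clinical measurements requires a rule that turns a measurement into an expected femur motion, skin strain or pressure, with a statement of how far off that value may be. A partial correlation is a symmetric, unit-free number. It has no slope, no intercept and no residual error in millimetres, strain or pressure units, and its size depends on how widely the sampled participants vary. The aim 1 model cannot fill the gap, because its inputs are the laboratory quantities that a clinic does not have.

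Two things are at stake. Followed as written, aim 2 hands over a list of associations where aim 3 expects predictions. And the retention rule asks whether an association exists and looks at least moderate, not whether the measurement predicts the mechanic closely enough to guide a design for one patient.

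**Working it through.** **Inputs.** n = 30 for aims 1 and 2, alpha .05, f² = 0.45 with three in-socket mechanics (Sample size {14}); four named covariates ({20a}, Aim 2); nine sockets per participant (Dynamic biplane radiography, under {18a}). Assumed: two-sided tests, linear and normal relations, and one record per participant, except in step 6.

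**1. The plan's own figure.** For an overall F test with u = 3, v = n − 4 and noncentrality f² × n, power is 0.810 at n = 29 and 0.827 at n = 30. The stated n = 30 therefore reproduces. The effect corresponds to R² = 0.45/1.45 = 0.31. This sizes the three-mechanic model; no separate figure is given for the aim 2 correlations.

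**2. Smallest significant partial correlation.** df = 30 − 2 − 4 = 24 and t = 2.064. Then r = t/√(df + t²) = 2.064/√(24 + 4.260) = 0.388.

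**3. What a retained r is worth for prediction.** The SD left after covariate adjustment is multiplied by √(1 − r²):

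| partial r | share of adjusted variance explained | SD ratio | reduction in SD |
|---|---|---|---|
| 0.388 | 15% | 0.922 | 8% |
| 0.5 | 25% | 0.866 | 13% |
| 0.7 | 49% | 0.714 | 29% |

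These reductions apply to the covariate-adjusted mechanic, not to its raw spread.

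**4. Precision and selection.** The Fisher-z 95% interval, with standard error 1/√(30 − 4 − 3), is 0.14 to 0.74 for an observed r of 0.5. In a simulation of 100,000 samples at 24 df, a true partial r of 0.3 reached significance 32% of the time, and the mean observed |r| was then 0.49. Selecting on significance makes a modest relation look stronger than it is.

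**5. Dependence on the sample.** Keep the slope and error that give r = 0.5, and halve the spread of the clinical measure. Then r = 0.5 × 0.5/√(0.25 × 0.25 + 0.75) = 0.25/0.901 = 0.28. The relation is equally usable, but it would fall below the 0.388 threshold.

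**6. If records per socket were used.** 30 × 9 = 270 records. Treated as independent (an assumption; the protocol does not say so), the significance threshold falls to |r| = 0.12.

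**7. Tracing the predicted values.** Aim 1 gives mechanics → outcomes, as a model. Aim 2 gives clinical measurement ↔ mechanics, as a correlation. Aim 3 needs clinical measurement → prediction, with observed values regressed on it. The middle link is never estimated as an equation.

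**The case against.** Aim 2 is framed as an association aim, and partial correlation suits that. Screening by association and building the model afterwards is a sensible order; the title of aim 3 itself speaks of development, and a condensed article may leave the bridging step to the full protocol. The trial is labelled exploratory and its third aim a pilot. These points limit how serious the matter is. They do not remove it, because the article does not merely leave the step out: it says the predictive model comes from aims 1 and 2, fixes the aim 2 method and fixes the hand-over rule, and these do not fit together.

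A reader might infer that weak predictors will be carried forward. The text does not support that. The rule asks for correlations that are both moderate-to-strong and significant, and no document says that 0.39 qualifies as moderate. Such measurements can be retained; it is not established that they will be.

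A reader might also infer that prediction is never checked. It is: the protocol plans an out-of-sample comparison in 15 new participants. That check still needs predicted values from somewhere. It also includes sockets already made by the new process, so as described it does not screen predictors before they are used.

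Finally, the protocol states no accuracy target, so the SD reductions describe what the rule admits and not a breach of a stated standard.

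**Conclusion.** The point holds: the aim 2 method does not supply what aim 3 is said to use, and the retention rule is not tied to predictive accuracy. Measurements that barely narrow the prediction can pass: an 8% reduction in covariate-adjusted SD at the significance limit, and 13% at r = 0.5. These sizes rest on one record per participant, n = 30, all four covariates and linear, normal relations; with several sockets per person the threshold depends on how clustering is handled. The protocol should be changed before the aim 2 analysis, but in an exploratory study this is a correctable choice of method. It does not undermine aim 2 as a study of association.

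**What to change.** In aim 2, replace the partial correlation with a regression of each in-socket mechanic on the clinical measurement plus the covariates. Use a participant-level random effect or clustered errors wherever several sockets per person enter. With one record per person and the same covariates, the test of the coefficient is identical to the partial-correlation test, so nothing is lost on the association question.

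Report the slope, intercept and residual SD in the units of the mechanic, and the leave-one-participant-out prediction error. To judge predictive value, compare models with and without the measurement over the same clinic-available covariates; CT-derived femur length should be in both models or in neither. Decide retention on the change in cross-validated error alongside the significance test. Carry the fitted equation and its error into aim 3, and state how it links to the aim 1 model.

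The cost is revised analysis wording and a little more programming on the same data. The retention decision does change, and fewer measurements may go forward.

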#### Specific aim 1: Determine the relationship between in-socket mechanics and patient-reported comfort and function

The purpose of this aim is to reveal how in-socket mechanics, that is, (1) residual femur motion relative to the socket, (2) skin strain, and (3) pressure distribution, are related to socket design and patient-reported comfort and function. We hypothesize that (H1) the amount of residual bone motion, (H2) the peak rate of skin strain, and (H3) the peak pressure within the socket are associated with patient-reported comfort and function.

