### Interventions

#### Explanation for the choice of comparators {6b}

Every participant in aims 1 and 2 will be fitted with several different check-sockets for this study, each deliberately modifying one of the independent variables: brim height, volume, cross-sectional geometry, and material stiffness. These variables are known to have an effect on the comfort and function of the socket, and they are among those routinely altered in the static and dynamic fitting process [33]. Those modifications are generally iterative and performed in conjunction with others. For instance, changes in the geometry such as the oblique medio-lateral dimension at the perineum by padding the area of the ischial containment level will also affect the volume of the socket as well as the material stiffness in the modified region. The degree of modifications and manner of combinations is very much customized and informed by individual characteristics such as soft tissue content and pain tolerance. For the study, in order to standardize interventions as much as possible and minimize the risk of drastically compromised socket fit, we will make well-defined modest changes using the participants’ original (current) sockets as the baseline. One single prosthetist will facilitate all the modifications to assure consistency across the sample.

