### Outcomes {12}

Outcomes for each participant will be averaged across three trials for each of the interventions, to analyze the change from baseline with different socket designs.

Many of the assessment methods are identical or equivalent to clinical assessment instruments that are associated with high validity and low risk for the target population. The effective radiation dose due to dynamic biplane radiography is estimated to be 2.0 mSv or less for the 27 trials collected for each participant. For comparison, the average effective dose associated with a knee CT scan from our previous studies was 1.4 mSv, and in the USA, we receive about 3.0 mSv of exposure from natural background radiation every year [37].

The following is the primary outcome variable:
*Socket comfort*

The following are the secondary outcome variables:
*Hip range of motion (ROM)**Three-dimensional (3D) skin motion within the socket**Residual femur position within each socket**In-socket pressure**Plantar pressure**Ground reaction forces during gait**Overall body motion (e.g., trunk lean, hip flexion/extension) during gait*

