### Assignment of interventions: allocation

#### Sequence generation {16a}

The order of the modified sockets worn by each participant will be randomized using computer-generated random numbers.

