### Methods for additional analyses (e.g., subgroup analyses) {20b}

Not applicable, as no additional analyses are part of the protocol.

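### Aim 3 relies on a socket modification model from aim 1, but no model specified for aim 1 contains socket modification

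*Protocol article*

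**What the plan says.** **Purpose.** Specific aim 1 is to show how residual femur motion, skin strain and pressure "are related to socket design and patient-reported comfort and function". The Specific aims overview likewise puts socket design in the aim 1 relationship. The three aim 1 hypotheses, however, link mechanics to comfort and function only.

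**Design.** Explanation for the choice of comparators {6b} names four independent variables: brim height, volume, cross-sectional geometry and material stiffness. Each participant wears every variant. On sequence, the article says: "The order of the modified sockets worn by each participant will be randomized".

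**Analysis.** Under Aim 1 in Statistical methods {20a}, the generalized linear model assesses "The effects of in-socket mechanics, such as residual bone motion, peak skin strain, and pressure distribution on both physical function and patient-reported outcomes". The unified model keeps the significant parameters of that model. Aim 2 uses partial correlations between mechanics and clinical measurements. Aim 3 then states: "we will use empirical data to test the socket modification model(s) created in aim 1". It also compares two design methods by Wilcoxon-Mann-Whitney.

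**By socket design.** Outcomes {12} says outcomes are averaged per intervention "to analyze the change from baseline with different socket designs", with no model or test attached.

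**Reference.** Section {6b} speaks of making modest changes with the "original (current) sockets as the baseline". The global ratings of comfort and function in {18a} are also made relative to the current socket.

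**The concern.** A process that selects socket changes needs two links: from modification to mechanics, and from mechanics to comfort and function. The specified model supplies the second only. It can say that less femur motion or lower peak pressure goes with better comfort. It cannot say which change in brim, volume, geometry or stiffness moves which mechanical parameter. The Background, under Critical needs, gives that question as a reason for the study.

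The mechanics are measured, not assigned, so their association with comfort is observational even within a participant. The socket variants are the manipulated factor, worn by everyone in random order, and they support the better-controlled comparison. If the plan is followed as written, part of aim 1 goes unanswered and aim 3 cites a model that was never fitted.

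The choice of reference is a second, separate issue. The brim variants are cut from the PETG copy and the volume variants are also PETG. Acclimation to each socket lasts up to 5 minutes, whereas the current socket is the one the participant normally wears. Variant minus current therefore mixes the modification with copying, check-socket material and familiarity.

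**Working it through.** **1. Terms in each specified analysis (Statistical methods {20a})**

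| Analysis | Response | Explanatory side | Socket modification? |
|---|---|---|---|
| Aim 1 GLM | function, patient-reported outcomes | femur motion, skin strain, pressure | no |
| Aim 1 unified model | function, patient response | significant terms of the GLM | no |
| Aim 2 partial correlation | mechanics paired with clinical measures | limb length, soft tissue and similar covariates | no |
| Aim 3 model test | observed values | predicted values | no |
| Aim 3 comparison | patient-reported outcomes, cost | design method | no |

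Set against this are the aim 1 purpose and the aim 3 sentence, both of which presuppose a model with socket design in it.

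**2. The plan's own sample size.** Inputs from Sample size {14}: n = 30, f² = 0.45, α = 0.05, 80% power, three mechanics. I used the overall F test with noncentrality λ = f²·n and df = (3, n − 4), one row per participant.
- n = 30: λ = 0.45 × 30 = 13.5, df = (3, 26), power 82.7%.
- n = 28: 79.2%. n = 29: 81.0%. The minimum is 29, so the stated 30 reproduces.
- With a fourth predictor at n = 30, df = (4, 25), power is 77.0%.

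The stated figure fits a model holding the three mechanics and nothing else. That agrees with step 1 but does not prove it.

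**3. Conditions available.** Two unmodified copies (PETG, EVA) + 2 brim + 2 volume + 2 geometry = 8 check sockets. Adding the current socket gives 9, and 9 × 3 trials = 27, as Outcomes {12} states. The unmodified PETG copy is therefore among the sockets tested. Taking it as reference leaves 8 − 1 = 7 contrasts.

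**4. What 30 participants can detect for one within-participant contrast.** Paired t test, df = 29, noncentrality d·√30, two-sided.
- α = 0.05: critical t = 2.045, 80% power at d = 0.529.
- α = 0.05/7 = 0.00714: critical t = 2.894, 80% power at d = 0.688. Power at d = 0.529 falls to 51%.

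Here d is the mean within-participant difference divided by the SD of those differences. The documents give no such SD for the mechanics, so d is not converted to millimetres or strain.

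**5. The reference.** For a brim or volume variant:

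variant − current = (variant − PETG copy) + (PETG copy − current)

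The second bracket carries copying, material and familiarity. Its size is not given in the documents. All three sockets are measured, so the first bracket can be recovered by subtraction.

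**The case against.** The strongest reply is that the stated aim 1 hypotheses concern mechanics against comfort and function, and the GLM answers them. The modifications are then a device for creating variation in the mechanics. Model detail for the socket-design analysis announced in Outcomes {12} may sit in the full protocol or a statistical analysis plan, and the trial calls itself exploratory. This bears on severity, but it does not reconcile the aim 3 sentence with the aim 1 model: the article describes the aim 1 model, and it is not a model of socket modification.

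Several stronger readings are tempting and are not supported:
- **That modification is in no planned analysis.** Outcomes {12} announces one; what is missing is a method.
- **That a randomised comparison is discarded.** Only the order of sockets is randomised; modification is a condition everyone receives. Implementation {16c} also applies random order to the aim 3 phase, which does have a planned comparison.
- **That further analysis is ruled out.** The statement that "no additional analyses are part of the protocol" stands under an item whose example is subgroup analyses. It does not cancel what {12} announces.
- **That aim 3 has nothing to test.** The mechanics-to-outcome model and the aim 2 correlations remain.
- **That the choice of reference causes the gap or biases a planned estimate.** It is a separate matter. In {6b} baseline describes how variants are made, {12} does not say which socket it means, and no brim or volume contrast is written out.

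**Conclusion.** The point stands as an internal contradiction between the aim 1 purpose and the aim 3 text on one side and the aim 1 model on the other. What is missing is the design-to-mechanics link only. No reported figure is wrong, and the sample size reproduces for the model actually described.

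The reference problem is conditional: it arises if baseline in Outcomes {12} means the current socket. It is recoverable, because the PETG copy is tested. The PETG copy is an assured reference for the brim and volume variants and for the EVA-versus-PETG stiffness contrast. It is not assured for geometry, because the article does not state the material of those sockets.

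The detectable differences of about 0.53 (one unadjusted contrast) and 0.69 (Bonferroni for seven) assume 30 complete participants and a paired t approximation. They make no allowance for the several mechanical parameters and outcomes.

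**What to change.** Add to Aim 1 in Statistical methods {20a}:

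- A mixed model for each mechanical parameter, and for comfort and function, with socket condition as fixed effect, participant as random effect and test position as covariate.
- The unmodified PETG copy as reference for the brim, volume and EVA (stiffness) contrasts. Use it for the geometry contrasts only if those sockets are also PETG, and state their material.
- The PETG copy versus current socket difference, reported separately as the effect of copying, material and familiarity.
- All contrasts reported as exploratory, with confidence intervals.

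State in Outcomes {12} which socket baseline means. In the aim 3 text, name this model as the design-to-mechanics part of what is tested. The minimum alternative is to reword that sentence to name the mechanics-to-outcome model that aim 1 builds, and to limit the claim about socket design accordingly.

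The cost is protocol wording and analysis time. No new sockets, visits or measurements are needed.
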